## Methods

### Study Design

This study is a parallel RCT with 3 groups: a group receiving the self-help book with weekly asynchronous and tailored email support (TL-E); a group receiving the self-help book without email support but with a weekly information email (TL-I); and a waiting list control group (WL). Outcomes will be assessed at baseline (T0), post-test (around 3 months after baseline; T1), and at 6 (T2) and 12 months (T3) after baseline. All measurements will be self-reported and gathered via email with a link to a personal questionnaire built with Qualtrics software [42]. The design and procedures of this study were approved by the Ethics Committee of the University of Twente in The Netherlands (no. 13212).

### Participants

Participants will be recruited from the general population in The Netherlands using newspaper advertisements. The recruitment messages will be positively framed: (1) “Get the best out of yourself and improve your resilience and well-being with a free self-help course”, and (2) “Become happy and stay happy? Improve your resilience and well-being with a free self-help course”.

Interested participants will be directed to a website with extensive information about the study and an application form. After applying, participants will be sent a personal link to a screening questionnaire on their specified email address. Participants who open the personal link will be asked to give online informed consent. If no informed consent is given, participants will be diverted to the information website and will not be able to participate in the study. If informed consent is given, participants will fill out the screening questionnaire before the start of the study. Figure 1 shows the intended flow-chart of participants.

Adults aged 18 or above with low or moderate levels of well-being without moderate or severe clinical symptomatology are eligible for this study because previous studies have shown that these individuals might search for happiness [41] and could boost their mental health by elevating the level of well-being [7,8]. Other inclusion criteria are a sufficient internet connection, a valid email address, and a willingness to invest an average of 4 hours per week for 8-12 weeks. In the screening questionnaire, the Mental Health Continuum Short Form (MHC-SF) will be used to assess the level of well-being and the Hospital Anxiety and Depression Scale (HADS) will be used to assess the level of clinical symptomatology. Participants will be excluded from the study if they score 4 or 5 (range 0-5) on at least 1 of the 3 emotional well-being items in combination with a score of 4 or 5 (range 0-5) on at least 6 of the 11 social and psychological well-being items of the MHC-SF, which is operationalized as flourishing (ie, high levels of well-being) [13,43]. Participants will also be excluded if they score 10 or higher (range 0-21) on the depression scale and/or on the anxiety scale of the HADS, which indicates individuals with moderate or severe clinical symptomatology [44]. Participants who will be excluded from the study will be notified by email because, (1) they are already flourishing, or (2) they probably have at least moderate depression or anxiety symptoms. The latter group will receive their specific scores and their meaning on the HADS and will be advised to talk to their general practitioner when symptoms persist or increase. After screening, the remaining participants receive a personal email link to the baseline questionnaire.

**Figure 1 figure1:**
[figure not shown]
Design of the study and intended flow-chart of participants.

### Randomization

Randomization will be conducted after all eligible participants complete the baseline questionnaire, with 396 participants being randomly assigned to 1 of the 3 groups (allocation ratio, 1:1:1). Randomization will be stratified by gender and educational level (ie, low, medium, high) using a computerized random number generator created with Excel. This is an automated process with no interference from the investigators.

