#### Primary Outcome

Well-being is the primary outcome of this study, measured with the 14-item MHC-SF and the 8-item Flourishing Scale (FS). The items of the MHC-SF can be divided into 3 subscales: emotional well-being (3 items), social well-being (5 items), and psychological well-being (6 items). All items can be answered on a 6-point answer scale from 0 (never) to 5 (almost always). A mean score will be computed separately for the total scale and the 3 subscales. The MHC-SF has excellent psychometric properties [5,13]. The FS measures social-psychological well-being with 8 positively formulated items. Participants rate the items on a 7-point scale from 1 (strongly disagree) to 7 (strongly agree). Total summed scores can range from 8-56. The FS has demonstrated good internal consistency and construct validity [69].

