### Sample Size

Well-being is the primary outcome used for the power calculation. We expect to detect a significant effect on well-being between the experimental groups TL-E and TL-I compared to the WL group. Based on recent meta-analyses [17,18] and a previous comparable study [38], we expect to find a standardized effect size on well-being of 0.40 or larger. The targeted sample size is 99 participants per group (297 in total) to provide a statistical power of (1 - *β*) = 80% and a 5% significance level (two-tailed). To allow a study dropout rate of 25%, we need 132 participants in each condition and 396 participants in total for the trial.

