### Statistical Analyses

The Consolidated Standards of Reporting Trials (CONSORT) statement [91] will be used to report the results. Independent *t* tests and Chi-square statistics (X^2^) will be used to examine baseline differences between the study groups. Non-significant socio-demographic differences at baseline will indicate successful randomization. Internal consistency of the constructs will be determined using Cronbach’s alpha. To examine the efficacy of the intervention, intention-to-treat analyses will be conducted by including all participants in the analyses who have been randomized. The Expectation Maximization (EM) method will be used to impute all missing data on the continuous measures of T1, T2 and T3. This method imputes the data by maximum likelihood estimation using the observed data in an iterative process [92]. The intention-to-treat analysis will be compared with a completers-only analysis.

To examine significant differences between the 3 groups, we will perform repeated measures ANOVA in a 3 (group) x 3 (time) design with well-being (MHC-SF and FS) as the primary dependent variable and positive/negative emotions (mDES), the use of strengths (SUS), optimism (LOT-R), self-compassion (SCS-SF), resilience (BRS), and positive relations with others (SPR) as the secondary dependent variables. Significant time x group interactions will be tested with Tukey’ post hoc tests. Within-group effects (Cohen’s *d*) will be calculated by subtracting the mean post-test or follow-up score from the mean baseline score and dividing the difference by the pooled standard deviation. Between-group effects (Cohen’s *d*) will be calculated by subtracting the mean post-test or follow-up score of the experimental group from the mean post-test or follow-up score of the control group, and dividing the difference by the pooled standard deviation [93]. These effect sizes are used to gain insight into the relevance of the significant effects. To examine changes in the amount of flourishers, languishers, and moderately mentally healthy (MHC-SF), descriptive statistics will be used. Changes in categories will be tested with X^2^-statistics.

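### Well-being at T0 is known for everyone before allocation, but it is neither a stratification factor nor adjusted for in the between-group Cohen's d, which costs precision without biasing the trial

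*Protocol article*

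**What the plan says.** Under Randomization: "Randomization will be conducted after all eligible participants complete the baseline questionnaire, with 396 participants being randomly assigned to 1 of the 3 groups", with "allocation ratio, 1:1:1" as the ratio. The strata are given as "Randomization will be stratified by gender and educational level (ie, low, medium, high"). Baseline well-being is not among them.

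Under Primary Outcome: "Well-being is the primary outcome of this study, measured with the 14-item MHC-SF and the 8-item Flourishing Scale (FS"). Study Design and Table 2 place both scales at T0, and Table 2 also has the MHC-SF at screening. Both primary scores therefore exist for every participant when the list is drawn.

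Under Statistical Analyses, the between-group d is "calculated by subtracting the mean post-test or follow-up score of the experimental group from the mean post-test or follow-up score of the control group", divided by the pooled standard deviation. It has no baseline term, whereas the within-group d does use the baseline mean. Efficacy is tested by a 3 (group) x 3 (time) repeated measures ANOVA, read through the time x group interaction. The effect sizes are then used to judge the relevance of significant effects. Baseline differences between groups are to be tested, but the criterion for successful randomization refers only to socio-demographic variables.

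**The concern.** The baseline value of the outcome is usually among the best predictors of its later value. Here it is available for all participants before allocation, and neither the design nor the reported effect size uses it. Two consequences follow.

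- The between-group d carries avoidable random error. If one arm happens to start higher, part of that head start appears in d.
- The test and the effect size treat the head start differently. The interaction works on change from T0 and the raw d ignores T0, so the same imbalance pushes the two in opposite directions. A reader who uses d to judge the relevance of a significant interaction may then see two figures for one contrast that do not fit together.

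**Working it through.** **Inputs.** From Sample Size: d = 0.40, two-sided 5%, power 80%, 99 per group, 25% dropout, 132 per group, 396 in total. From Randomization: 1:1:1, gender (2) by education (3). The baseline to follow-up correlation r is not given; 0.5 to 0.7 is assumed, with 0.4 and 0.8 as outer values. Scores are put in SD units, with equal SD at both times and complete data. Differences are taken as experimental minus control; the protocol's order of subtraction only reverses the sign.

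**1. The plan's own figure.** n = 2 × (1.960 + 0.842)² / 0.40² = 98.1, so 99 per group. 99 / (1 − 0.25) = 132, and 3 × 132 = 396. The stated numbers reproduce.

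**2. Chance imbalance at T0.** The SD of the difference between two arms is √(2/132) = 0.123. The 95% range is ±1.96 × 0.123 = ±0.24 SD. The chance of exceeding 0.20 SD, half the planned effect, is about 10% for one pair of arms. It is about 18% for at least one of the two comparisons with the waiting list (simulation). For completers only, at 99 per arm, the SD is √(2/99) = 0.142 and the range ±0.28.

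**3. Carry-over of an imbalance D.** With true effect δ, the expected raw follow-up difference is δ + rD. The expected difference in T0-T1 change is δ − (1−r)D. The gap between them is D.

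| D | r | Shift in raw d | Shift in change contrast |
|---|---|---|---|
| 0.20 | 0.5 | +0.10 | −0.10 |
| 0.20 | 0.7 | +0.14 | −0.06 |
| 0.24 | 0.5 | +0.12 | −0.12 |
| 0.24 | 0.7 | +0.17 | −0.07 |

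At D = 0.24 the shift in raw d is 30% to 42% of the planned 0.40. At r = 0.4 and 0.8 it is 0.10 and 0.19.

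**4. How often the two figures part company.** Take one experimental arm against the waiting list, true d = 0.40, and a simple T0-T1 change test. The raw difference has standard error 0.123, the change difference 0.123 × √(2(1−r)), and their correlation is √((1−r)/2). From the bivariate normal:

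- significant change test with raw d below 0.20: about 3% of trials (r = 0.5) to 5% (r = 0.7);
- non-significant change test with raw d above 0.30: about 5% (r = 0.5) to 0.5% (r = 0.7).

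**5. Adjusting d for T0.** The standard error becomes 0.123 × √(1−r²).

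| r | Raw SE | Adjusted SE | Variance saved (r²) |
|---|---|---|---|
| 0.4 | 0.123 | 0.113 | 16% |
| 0.5 | 0.123 | 0.107 | 25% |
| 0.7 | 0.123 | 0.088 | 49% |
| 0.8 | 0.123 | 0.074 | 64% |

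The adjusted d no longer moves with D. The change contrast still does, so the gap shrinks from D to (1−r)D: for D = 0.20, from 0.20 to between 0.10 and 0.06.

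**6. Stratifying on T0 instead.** In simulation, T0 tertiles as a stratum cut the SD of the imbalance from 0.123 to about 0.055 to 0.060. The variance of the raw d then falls by about 19% (r = 0.5) to 38% (r = 0.7), less than the 25% and 49% from adjustment alone.

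**The case against.** The strongest reply is that the plan contains no error of validity, and this stands. Choosing gender and education as strata is legitimate, and the Discussion explains it by the expected excess of highly educated women. Chance imbalance is random error already included in the standard error of the post-test difference, so over repeated trials the raw d averages the true effect. A reader might infer that the missing stratum biases the trial, or that a baseline difference passes in full into the reported effects. The documents support neither reading. Only the fraction r carries over, and only into the between-group d; the within-group d and the interaction both use T0.

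It is also fair that d has a descriptive role after the test, that the planned baseline comparisons could expose a large imbalance, and that clear clashes between test and effect size are uncommon (step 4). Excluding flourishers on the MHC-SF restricts the T0 range and may lower r, which would reduce both the carry-over and the gain from adjustment.

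Against re-stratifying, MHC-SF tertiles would leave out FS and create up to 2 × 3 × 3 = 18 cells, some of them sparse if few men or few people with low education enrol.

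The reply that an adjusted estimate may sit in an unseen analysis plan does not fully answer the point. The protocol does not leave the between-group d open; it fixes a formula, and that formula has no baseline term.

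**Conclusion.** The point holds as a loss of precision in a reported effect size. It is not a flaw in the allocation or a source of bias. With 132 per arm, the chance T0 difference has an SD of 0.123. An imbalance of 0.20 SD, expected in about 10% of single contrasts, moves the raw d by 0.10 to 0.14 and a T0-T1 change contrast by 0.10 to 0.06 the other way. Adjustment would save 25% to 49% of the variance of d. These figures rest on an assumed r of 0.5 to 0.7, equal SDs over time and complete data. The opposite shift is exact for a two-time-point change contrast, which only stands in for the 3 x 3 interaction. A reader might go further and conclude that the randomization must be redone with well-being as a stratum; that does not follow, because adjustment recovers more precision than tertile strata would.

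**What to change.** In Statistical Analyses, define the between-group d for MHC-SF and FS at each post-test or follow-up time as the T0-adjusted mean difference divided by the pooled unadjusted SD. Use an ANCOVA-type model with each outcome adjusted for its own T0 score. Keeping the unadjusted SD leaves d on the same scale as the planned 0.40. The raw d can be shown beside it for comparison with other studies.

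The cost is one sentence. It needs no new data, no change in sample size and no change to the randomization. Adding T0 MHC-SF to the strata under Randomization is optional; if it is done, sparse cells need a stated merging rule, and d should still be adjusted for T0.

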### Interventions

This study will use the self-help book, “This is your life” [40] in both experimental conditions. This book is mainly based on the overarching and comprehensive well-being theory of Seligman [10] and Ryff’s theory of psychological well-being [19]. The book consists of 8 modules on 6 key components in positive psychology: positive emotion; discovering and using strengths; optimism and hope; self-compassion; resilience and post-traumatic growth; and positive relations (Table 1). Each module contains psycho-education derived from specific theories and empirical evidence in positive psychology and related research areas. Each module also contains a number of positive psychology exercises, ranging from 3-10 per module. Most of these exercises are evidence-based, such as the "three good things exercise" [17,18] and "imagine your best possible self" [45-47]. All modules are, in theory, effective independent strategies for enhancing well-being. Participants in the experimental groups will receive the self-help book by regular mail, accompanied by a time schedule for reading the book and practicing the recommended exercises (see Table 1). Participants will be instructed to read one module per week—except for module 2, which can be spread out over two weeks—in sequential order, and to practice the recommended exercises of that module. If the participant has more time, he or she can re-read the module and practice other exercises of that module. Participants will be encouraged to invest the most time in the exercises that feel most beneficial to them. Participants will have 8-12 weeks to complete the 8 modules of the book to take holidays and other circumstances into account. When participants in the TL-E group need more than 9 weeks to complete the book, in consultation with the counselor, they will not receive email support in the weeks they are not in the position to work on a module. Participants in the TL-I group will receive weekly information emails during the first 9 weeks and will be asked to read the emails in chronological order in the weeks they actually work on a module. On average, participants in the experimental groups will be expected to invest 4 hours per week during the intervention period.

**Table 1 table1:** Content of “This is your life” and recommended exercises for participants in the experimental conditions.

Module	Recommended exercises	Theoretical background
1. Positive emotions	Diary of pleasant emotions: What happened, who was there, what did you feel, what did you thought?	Fredrickson, 1998 [48]; Fredrickson, 2001 [49]; Fredrickson, 2009 [50]
	Three good things: Think about three things that went well today and savor those moments.	
2. Discovering strengths	Overview of your strengths: Which of the 47 strengths do you have and which of these give you energy and pleasure?	Linley et al., 2010 [51]; Linley and Harrington, 2006 [52]
	Identify your strengths I: Answer the 10 questions (ie, who inspires you?) that will help you to discover your strengths.	
	Identify your strengths II: Which strengths do you recognize in answering the 10 questions?	
	Vision of others: Ask 3-5 people about your top 5 strengths with examples from daily life.	
	Top 5 strengths: Based on all previous exercises, choose your top 5 strengths that also give you energy and pleasure.	
		
3. Use of strengths, flow	Change “must” into “want”: Make a list of things you don’t like but must do. What are underlying intrinsic motivations?	Csikszentmihalyi, 2001 [53]
	Flow: Have you experienced flow and why?	
	Flow at the moment: How much flow did you experience the preceding week? When, how?	
	Challenge yourself: How can you create more flow in your life? Use your strengths in a new way.	
		
4. Optimism, hope	ABC-Diary: What do you think and do when something negative happens? How can you challenge favorite pessimistic thoughts?	Carver et al., 2010 [54]; Scheier and Carver, 1992 [55]; Seligman, 1990 [56]
	Imagine your best possible self: Visualize yourself in the personal, relational, and professional domain.	
		
5. Self-compassion	Wish yourself something good: Be mindful and identify your greatest need at this moment. Use your inner voice to repeat your compassionate wish.	Gilbert, 2009 [57]; Neff, 2003 [58]; Neff and Germer, 2012 [59]
	Develop a compassionate inner voice: Write 5 minutes about situations in the preceding week wherein you showed self-compassion.	
		
6. Resilience	Coping style: Take the test to identify your prominent coping style(s).	Joseph, 2011 [60]; Joseph and Linley, 2006 [61]; Tedeschi and Calhoun, 2004 [62]
	Expressive writing: Write 15 minutes on at least 4 days about emotions, thoughts, and feelings around a negative or positive event.	
	Needs: What are your specific needs at this moment? Who should know your needs?	
		
7. Positive relations (I)	Active-constructive responding: Respond positively to good news shared by others. Use active communication skills, how does the other react?	Gable et al., 2004 [63]; Reis and Gable, 2003 [64]; Reis et al., 2010 [65]; Rosenberg, 2009 [66]
	Listen compassionately: Try to use elements of compassionate listening, such as “What feelings and needs does the other express?”	
	Expressing gratitude: Write a gratitude letter and/or read it aloud to the person you are thankful to.	
		
8. Positive relations (II)	Relaxation/meditation: Relax by doing a “body scan”, physical exercise, or “stand like a tree”.	Bloom, 2011 [67]; Otake et al., 2006 [68]
	Reflect on your needs: What are your intrinsic goals, needs and motives? Do you live those needs and why (not)?	
	Acts of kindness: Rejoice somebody by performing an unexpected act of kindness or by doing volunteer work.	

#### Email Support

The TL-E group will receive weekly email support from a personal counselor. These counselors will be 5 senior positive psychology students of the University of Twente who completed a course on email counseling in which they are trained to guide a fellow student on using the self-help book “This is your life”. Each of these will guide 25 participants and the remaining participants will be guided by the first author (MS). Participants will be randomly assigned to 1 of the 6 counselors in the same manner as the randomization procedure outlined above (eg, stratified by gender and educational level). Additional training will be given in a 1-day workshop and via weekly supervision by authors MS and EB and a clinical psychologist. In these meetings, random emails of the counselors will be discussed to increase treatment integrity, and counselors can ask specific questions to the supervisors. The personal counselors will introduce themselves in an initial email sent the day participants receive the self-help book. The participants will be asked to introduce themselves before the email sessions start. Participants will be instructed to send a weekly email on Sunday or Monday wherein they write about their experiences with the scheduled module. Every Wednesday, the personal counselors will answer the emails.

The main goal of the email support is to encourage the participants to read the scheduled modules and practice the recommended exercises. The email support will be more process-oriented than content focused, and will be flexible within the boundaries of the structured time schedule. The personal counselors will be instructed to provide tailored feedback on progress and process using positive reinforcement, paraphrasing, and motivational interviewing techniques (eg, “I read that you have invested quite some time in the recommended exercises of this week.”; “Could it be helpful for you to practice this exercise more regularly?”; “What have you discovered when you performed the exercises?”). Specifically, counselors will use positive reinforcement for signs of awareness, insights, improvement and change (eg, “This seems a valuable experience for you, how exactly did you achieve that?; “What will be a next sign of progress?”; “That seems like a helpful thought to me.”). When there are reasons to assume that a participant has serious complaints, the participant will be referred to a general practitioner or a health care specialist. In an attempt to reduce intervention dropout, reminders will be sent to participants who do not send an email to their counselor. The first 2 reminders will be sent by the personal counselor, followed by up to 3 additional reminders sent by the researcher (MS). If a participant has completed more than 3 modules of the book, he or she will only receive reminders from their personal counselor. A final email with overall feedback on the process of the participant will be sent to all participants who complete at least 3 modules. This final email will be sent when the participant has completed all modules (between 8 and 12 weeks), when the maximum of 3 reminders has been reached by the personal counselor, or when participants are in week 12 of the study without completing all modules.

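### Only TL-E participants share counselors, but the planned ANOVA and the sample size treat everyone as independent; with any positive counselor correlation the TL-E standard errors are too small

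*Protocol article*

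**What the plan says.** The protocol article, Email Support, gives each TL-E participant a personal counselor. Five are senior students and the sixth is an investigator: "Each of these will guide 25 participants and the remaining participants will be guided by the first author". Allocation to counselors is random and stratified: "Participants will be randomly assigned to 1 of the 6 counselors in the same manner as the randomization procedure outlined above". Counselors answer each participant weekly with individual feedback and send the first reminders against dropout.

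Under Email With Information, TL-I participants get a common question-and-answer email from the investigator and are told not to reply. Under Control group, WL participants have no counselor at any stage.

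Statistical Analyses fixes the model: "we will perform repeated measures ANOVA in a 3 (group) x 3 (time) design", followed by Tukey post hoc tests. Counselor appears neither as a factor or random effect nor among the moderators.

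Sample Size states: "we expect to find a standardized effect size on well-being of 0.40 or larger". It arrives at 99 per group and then adds for dropout: "To allow a study dropout rate of 25%, we need 132 participants in each condition and 396 participants in total". No design effect is mentioned.

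**The concern.** This is a partially nested design: one arm is clustered by counselor and two are not. Participants who share a counselor may end up more alike than participants who do not, because the counselor delivers the very component that sets TL-E apart. A repeated measures ANOVA with group and time as its only factors accounts for correlation within a participant over time, but not between participants of one counselor.

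If that correlation is positive, variation between counselors enters the TL-E mean without entering its standard error. Two contrasts are exposed: TL-E versus WL, which the trial is powered for, and TL-E versus TL-I, the only one that isolates email support. The section This Study expects TL-E to be equivalent or superior to TL-I. An interval that is too narrow can therefore mislead in both directions, by overstating superiority or by making equivalence look better established than it is. A few strong or weak counselors could be read as an effect of email support.

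**Working it through.** **Inputs from the protocol.** d = 0.40, two-sided 5%, 80% power, 99 evaluable and 132 randomized per arm (Sample Size); six counselors, five with 25 participants each (Email Support).

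**Assumed input.** The counselor ICC is not given. The range 0.01 to 0.05 is an assumption.

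**1. The plan's own figure.** n per arm = 2(1.96 + 0.84)^2 / 0.40^2 = about 98, and 99 with the t distribution. Then 99 / 0.75 = 132, and 3 x 132 = 396. The stated figures reproduce exactly under independence, so they contain no allowance for clustering.

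**2. Cluster sizes.** The sixth counselor has 132 - 5 x 25 = 7. Effective cluster size m = (sum of squared sizes) / (sum of sizes):
- 132 per arm: (5 x 25^2 + 7^2) / 132 = 3174 / 132 = 24.05.
- 99 per arm, each caseload reduced by 25%: 24.05 x 0.75 = 18.03.

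**3. Formulas.** Design effect in TL-E: DE = 1 + (m - 1) x ICC. The comparison arm has DE = 1, so true SE / naive SE = R = sqrt((DE + 1) / 2), and the understatement is 1 - 1/R. The actual type I error of a test with critical value c is 2(1 - Phi(c / R)). For one unadjusted test c = 1.96. For Tukey with three groups c is about 2.35, a nominal per-comparison level of about 1.9%.

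**4. Results.**

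| Per arm | ICC | DE | R | SE understated | Type I, unadjusted 5% test | Type I, Tukey comparison (nominal 1.9%) |
|---|---|---|---|---|---|---|
| 132 | 0.01 | 1.23 | 1.056 | 5% | 6.3% | 2.6% |
| 132 | 0.02 | 1.46 | 1.109 | 10% | 7.7% | 3.4% |
| 132 | 0.05 | 2.15 | 1.255 | 20% | 11.8% | 6.1% |
| 99 | 0.01 | 1.17 | 1.042 | 4% | 6.0% | 2.4% |
| 99 | 0.02 | 1.34 | 1.082 | 8% | 7.0% | 3.0% |
| 99 | 0.05 | 1.85 | 1.194 | 16% | 10.1% | 4.9% |

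The 132 rows match the intention-to-treat set of all randomized participants; the 99 rows match the basis of the power calculation.

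**5. Simulation.** An unadjusted t test at one time point with 132 per arm and caseloads of 25, 25, 25, 25, 25 and 7 (20,000 runs per ICC) rejected in 4.8% of runs at ICC 0, 6.7% at 0.01, 7.5% at 0.02 and 12.1% at 0.05. This agrees with the formula.

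**6. Power for TL-E versus WL at d = 0.40, 99 evaluable per arm, correct SE.** Power = Phi(0.40 / SE - 1.96) with SE = sqrt((DE + 1) / 99):
- ICC 0: SE 0.142, power 80%.
- ICC 0.01: SE 0.148, power 77%.
- ICC 0.02: SE 0.154, power 74%.
- ICC 0.05: SE 0.170, power 65%.

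These use the normal approximation, as if the counselor variance were known. The penalty for estimating it from six clusters would lower them further.

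**The case against.** The protocol contains several features that point to a low ICC. All participants use the same book and schedule. Support is meant to address process more than content. The students took the same course, and a workshop and weekly supervision with review of sampled emails are added. Some reminders come centrally. Assignment to counselors is random and stratified. All this is fair, and at ICC 0.01 the effect is modest. But random assignment only prevents caseloads from differing at baseline; it does not remove similarity that arises later from sharing a counselor. Supervision may reduce that similarity, but the plan does not measure what remains.

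Inference could also be limited to these six counselors, in which case no correction would be needed. The Discussion supports this in part, since it leaves experienced professional counselors to future research. Yet it also addresses public mental health services, where other people would give the support. The premise of a wider pool is reasonable but remains a premise.

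A reader might infer that the trial's type I error is 6% to 12%. The protocol does not support that. Those figures belong to one unadjusted 5% test with 132 per arm, whereas the plan uses Tukey comparisons after a significant interaction. At the Tukey level the per-comparison error rises from about 1.9% to between 2.6% and 6.1%. The relative inflation remains.

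Finally, a condensed article may leave sensitivity analyses for counselor effects to an unseen analysis plan. That is true of the detail, but the article does name the primary model, and that model has no counselor term.

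**Conclusion.** The point holds conditionally. The nesting and the unadjusted model are both stated, and the sample size assumes independence. If the counselor ICC is above zero and the counselors stand for a wider pool, the standard errors of both TL-E contrasts are too small: by about 5% to 20% with 132 per arm, or 4% to 16% with 99, for an assumed ICC of 0.01 to 0.05. Power for TL-E versus WL falls from 80% to between 77% and 65%. TL-I versus WL is unaffected.

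It would go too far to say that the standard errors are wrong as a matter of fact. At ICC 0 the error vanishes, and the protocol gives no ICC. The figures also treat a comparison at one time point as a stand-in for the group x time analysis. The power loss should be read for TL-E versus WL only, because Sample Size bases its calculation on comparisons with WL and does not claim power for TL-E versus TL-I. The change is worth making before the data are analysed, but the point does not call the design itself into question.

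**What to change.** For every contrast that involves TL-E, replace the ANOVA with a partially nested mixed model, or at minimum report one beside it. The model should have:
- a counselor random effect in TL-E only, with each TL-I and WL participant as their own cluster;
- the repeated measures within participant kept in the model;
- Satterthwaite or Kenward-Roger degrees of freedom.

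Report the counselor ICC with its interval, and add a sensitivity analysis without the roughly 7 participants guided by the investigator. TL-I versus WL can stay as planned.

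No new data or staff are needed. Counselor assignment is produced by the randomization, and Process Outcomes says that the counselor correspondence is saved. The article does not list counselor as an analysis variable, so it should be named as one.

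The cost is real. This is a change of model and not one term added to the ANOVA. Intervals for TL-E contrasts will be wider, and a counselor variance estimated from six clusters, one of them very small, will be imprecise. An estimate near zero should therefore not be taken as proof that counselors do not matter.
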